**3.9 Development of the School CVD Risk Factor Reduction Intervention**

**Module for Secondary School Students**

Figure 3.2 shows a schematic diagram for the development of the school centered CVD risk factor reduction among public secondary school students module. The module will be developed through the process of consultations with group of experts. These will include experts from Universiti Putra Malaysia, the Ghana Health Service and expert teachers from Kintampo North and Nkoranza North districts. Their expertise will include; the area of public health, behavioral intervention, non-communicable diseases, and health education and promotion.

The training module will be developed for students which will serve as a guide for CVD risk factor reduction. CVD risk factor reduction module will be developed based on the Information-Motivation-Behavior Skills (IMB) model by Fisher and Fisher (1992) and divided into three sections. Table 3.1 shows how the IMB concepts will be addressed by the module. Session one is the general information phase. This includes the general overview of the knowledge of CVDs, its risk factors, types of CVD risk factors; modifiable (physical inactivity, smoking, alcohol, and unhealthy diet) and non- modifiable (such as age, gender, race, and ethnic background), how intermediary risk factors cause CVDs, how CVDs develop, and its prevention in terms of modifiable risk factors in the intervention schools. This will be carried out in the form of talks, workshops, and discussion sessions.

The second session will be the motivational phase. Students will be encouraged to perform the required physical activity on a daily basis, eat healthy foods, stop/not initiate smoking and alcohol and that healthy lifestyles would lead to being smart, healthy and free from obesity, diabetes, and being hypertensive. Students will be motivated that they would also be free from other diseases. They will also be encouraged to educate their peers. Poster, sport and dancing competitions, group work and interactions and role plays will also be carried out to motivate students.

Session three will be the behavioral skills phase. In this session students will be taught to demonstrate the ability to select their foods, to reduce sugar, and salt intake, to choose the appropriate fruits and vegetables, and the skills to perform the various forms of physical activities such as aerobic and anaerobic exercises, stop/not initiate smoking and alcohol consumption.

**Step 1:**

Consultation from experts in the area of public health, behavioral intervention, non-

communicable diseases, and health education and promotion

**Step 2:**

Development of the CVD risk factor reduction module among public secondary

school students based on the IMB Model

**Step 3:**

Presentation of the CVD risk factor reduction among public secondary school

student module draft to the experts

**Step 4:**

Improvement and modification to the CVD risk factor reduction among public

secondary school students module made

**Step 5:**

Final CVD risk factor reduction module among public secondary school students

produced

**Figure 3.2 : Steps Involve in the Development of the Intervention Module**

**Table 3.1 : Application of the Information-Motivation-Behavioral Skills Model for school based CVD risk factor reduction intervention module**

**IMB MODEL SECONDARY SCHOOL CVD RISK FACTOR**

**REDUCTION MODULE INFORMATION** Knowledge of cardiovascular disease and its risk

factors:

-Students will be informed how modifiable risk factors translates into intermediary risk factors and into CVDs

Prevention of CVDs through modifiable risk factors: Students will be taught on reduction of modifiable risk

factors of CVDs. These will include:

Physical Activity: Doing at least 60 minutes moderate to vigorous physical activity daily.

Diet: Consumption of healthy diet devoid of too much

salt, too much sugar, too much fat, too much fried foods, and red meat. Consumption of fruits and vegetables, drinking enough plain water instead of coloured (sugar) water, fish, whole grains instead of polished grains.

Smoking: Information on tobacco, stopping smoking (for student smokers) and not initiating smoking for non-smokers

Alcohol: Same with alcohol consumption as with smoking.

**MOTIVATION** Students will be encouraged that if they perform the required physical activity on daily basis and eat healthy foods they would become smart and healthy and would be free from overweight, obesity, diabetes, and being hypertensive. They would also be free from other diseases.

They will further be encouraged and taught that not initiating or stopping smoking and alcohol would make their lungs and heart function properly, strong, and free from heart diseases.

Peer groups to educate fellow students to serve as a source of motivation.

Poster, sport and dancing competitions, group work

and interactions, and role plays to motivate students.

**BEHAVIOURAL SKILLS** Students will be taught to demonstrate the ability to select their foods, to choose drinks with reduced sugar content, to reduce salt intake, to choose the appropriate fruits and vegetables, to know the skill to perform the various forms of physical activities (such as jumping jacks, hamstring, push-ups, squat, sit ups, and other aerobic exercises), stop/not initiate smoking and alcohol consumption.

**3.9.1 Validation of the Module**

The module will be reviewed by a panel of experts in public health, behavioral intervention, non-communicable diseases, and health education and promotion. The experts will give their consensus that the sections of the module will be valid in content, teaching methods and learning objectives.

**3.10 Training**

There will be two clinicians who will be involve in this study with specialty in public health. Also included will be twelve qualified health staff with Master’s degree qualification, and a physical education health instructor (with Diploma in Physical Education) who will implement the physical activity module of the intervention. All these staff are with the Kintampo Health Research Centre (Ghana Health Service). Clinicians, health staff, and PE health instructor will be selected if they had been involved previously in any of the Ghana Health Service field research. Health staff will be trained by the researcher and clinicians to take anthropometry (body weight and height) and blood pressure (diastolic and systolic BP) measurements. Health staffs (six) who will be involve in the baseline measurements will not take part in the post intervention measurements. Another set of six health staff will do the post intervention measurements to avoid observers’ bias. The objectives of the study will be explained to staff involved in the study. A week’s training will be organized for health staff on anthropometric and blood pressure measurements. The training of health staff will among other things to equip them to avoid inter and intra observer measurements biases.

The study has the involvement of school authorities. A week’s training will be organized for PE and other teachers in the intervention schools by the research team (researcher, clinicians, PE health instructor, and health staff). This will be done to ensure sustainability after the intervention to train new students. The study protocol including all measurements will be reviewed with the clinicians, health staff, physical education health instructor, and teachers before the commencement of the study.

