9. The behavioral modification intervention program will be effective in reducing the mean diastolic and systolic blood pressures among participants in the intervention group as compared to control group and also within the groups from baseline to six months among secondary school students in Brong Ahafo, Ghana.

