**3.8 Blinding**

This study is single-blinded. Health staff who will take measurements of students’ anthropometry and blood pressure measurements will be blinded to participants groups and will not take anthropometry and blood pressure measurements at the post-test intervention. Researchers and physical education health instructor who that will facilitate the health education and the physical activity modules respectively will not be blinded as such. Contamination of the study will be minimized since there will be intervention and control schools and that schools are far apart each other.

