**3.11 Intervention**

At this stage permissions and consent would had been sought from the Ministry of Education, District Directors of Education, Chairmen of the Parent Teacher Associations, parents/guardians, and students to carry out the study. All materials for the study will be ready at this stage. The objectives of the study and the eligibility criteria to participate in this study will be explained to all the students’ involved. Students will go through medical check-up which will be carried out by the two clinicians in order to pass eligibility criteria to be enrolled into the study.

The self-administered questionnaire will be given to students to complete. Health staff will measure students anthropometric and blood pressure measurements. Confidentiality and anonymity will be assured at all stages of the study. The module will be implemented in the intervention schools for a period of six months but not in the control schools. Then at the end of six months the same questionnaire will be given to students in both the intervention and the control schools. Health staff who will not take part during the baseline data collection will take anthropometric and blood pressure measurements of students at post intervention study. A total of 848 students will participate in the study; intervention (424) and the control (424) schools. Contamination of the intervention will be prevented by having intervention and control schools with distances between them.

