**3.13.4 Validity of the Anthropometric Measurement**

Anthropometric measurements in this study are weight, height, and blood pressure. All students in the study will be measured equally with the same weight, height, and blood pressure instruments. The study protocol procedures (including measurements of weight, height and blood pressure) will be reviewed with the study team through training sessions before the study will commence. The study instruments will be calibrated daily before use.

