**3.17.3 Inferential Statistics**

Chi-square tests will be performed to compare baseline characteristics of groups by their socio-demographic factors, family factors, CVD knowledge, motivation, behavioral skills, physical activity, smoking status, alcohol intake, BMI, systolic and diastolic BP. Independent t-tests will be performed to determine the between groups differences of total knowledge, motivation, behavioral skills, physical activities, dietary intake, BMI, diastolic and systolic BP. At six months post intervention, the independent and paired sample t-tests would be performed to determine the between and within group differences of variables respectively. Chi-square and the McNemar tests will also be performed on smoking status and alcohol intake at six months to determine the difference between and within groups since the variables are categorical variables.

A mixed design repeated measures analysis of variance (ANOVA) will be performed after checking that there is no substantial non-normality of residuals to determine the between and within group differences and its interactions on time differences on CVD knowledge, motivation, behavioral skills, physical activity, dietary intake, body weight, BMI, diastolic and systolic BP. Intention-to- treat (ITT) analysis will be the method that will be used to handle missing data in the analysis. Replacement of data will then be conducted for each missing variable using the multiple imputation method, following which Generalized Linear Mixed Model (GLMM) analysis will be performed to determine the overall effectiveness of the intervention study.

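### Replacing all six measurers at six months makes within-group change in weight, BMI and blood pressure inseparable from the change of team; the between-arm contrast is safe only if measurers are spread over all schools

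*Protocol*

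**What the plan says.** Three sections of the protocol agree that nobody measures at both visits.

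- Section 3.10 (Training): "Health staffs (six) who will be involve in the baseline measurements will not take part in the post intervention measurements", and then "Another set of six health staff will do the post intervention measurements to avoid observers’ bias".
- Section 3.11 (Intervention): "Health staff who will not take part during the baseline data collection will take anthropometric and blood pressure measurements of students at post intervention study".
- Section 3.8 (Blinding): the measuring staff "will be blinded to participants groups and will not take anthropometry and blood pressure measurements at the post-test intervention".

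No section says how the six staff of either wave are assigned to the four schools. The data form in Appendix A identifies school, student and district. Its Sections 9 and 10 have fields for weight, height and two blood pressure readings, but none for who took them.

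The within-group use of these measurements is explicit. Hypothesis 9 in section 1.6 states the expected benefit as follows: "reducing the mean diastolic and systolic blood pressures among participants in the intervention group as compared to control group and also within the groups". Hypothesis 8 has the same structure for weight and BMI, and objective 5 in section 1.5.2 also asks for change within groups from baseline to six months. Section 3.17.3 tests it: "the independent and paired sample t-tests would be performed to determine the between and within group differences of variables respectively".

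The protocol also takes steps that limit differences between observers. "A week’s training will be organized for health staff on anthropometric and blood pressure measurements", and section 3.13.4 adds that "All students in the study will be measured equally with the same weight, height, and blood pressure instruments", with daily calibration. Sections 3.12.3 and 3.12.4 script the measuring procedure, with a digital scale and an automated blood pressure monitor read twice.

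**The concern.** A before-after difference in one group contains everything that changed between the visits. Here the people who measure change completely and by design. If the second team reads systematically higher or lower than the first, every student's change carries that difference. More students make it look more certain; they do not average it out. A paired t-test cannot tell it from a programme effect, and it can hide a real change as easily as create a false one. Without a measurer code on the form, operator effects can be neither examined nor adjusted for afterwards.

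The second question is whether the same problem reaches the comparison of arms. That depends on how staff are distributed over schools, which the protocol leaves open. There are only two schools per arm, and section 3.8 describes the schools as far apart, so dividing staff by school would be a natural field arrangement.

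The outcomes concerned are secondary (section 3.15.2). They are the ones that staff measure and students do not report, and two of the nine hypotheses rest on them.

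**Working it through.** The protocol gives no operator variance and no figure to reproduce. The check uses its sample size and significance level together with assumed values.

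**Inputs**

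- Students per arm: 424 (section 3.11).
- Significance level: 0.05 (section 3.17), taken as two-sided.
- SD of a student's change in blood pressure: assumed 10 mmHg, range 8 to 12.
- Systematic shift between teams, b: assumed 0.5, 1 or 2 mmHg.
- SD between individual operators, t: assumed 0.5, 1 or 2 mmHg.

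**1. Within one arm, no true change.**

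SE = SD/√n = 10/√424 = 0.486 mmHg. With z = b/SE, the probability of a significant paired test is Φ(z − 1.96) + Φ(−z − 1.96).

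| Shift b | z at SD 10 | SD 10 | SD 12 to SD 8 |
|---|---|---|---|
| 0.5 mmHg | 1.03 | 0.18 | 0.14 to 0.25 |
| 1 mmHg | 2.06 | 0.54 | 0.40 to 0.73 |
| 2 mmHg | 4.12 | 0.985 | 0.93 to 0.999 |

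For scale, the systolic effects cited in sections 1.1 and 2.6.6 are −0.8 and −1.64 mmHg.

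**2. Between arms, measurers of each wave spread equally over the schools.**

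Each arm's mean change contains the same team shift b, so the difference in change contains b − b = 0. Simulation with 40,000 runs per setting gave type I error of 0.048 to 0.051 for t = 0.5, 1 and 2 mmHg. Spreading the staff does not help the paired tests, because within an arm visit and team still coincide.

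**3. Between arms, a separate three of the six measuring each arm in each wave.**

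The variance of an arm's operator mean in one wave is t²/3. Two waves give 2t²/3 for the change, and two arms give 4t²/3 for the difference in change. The added SD is √(4/3) × t = 1.15t. The student-level SE of that difference is 10 × √(2/424) = 0.69 mmHg.

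| Operator SD t | Added SD | Type I error |
|---|---|---|
| 0.5 mmHg | 0.58 mmHg | 0.13 |
| 1 mmHg | 1.15 mmHg | 0.32 |
| 2 mmHg | 2.31 mmHg | 0.58 |

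This uses the student-level standard error alone, so that it isolates the operator contribution. It describes an allocation of staff that the protocol does not state.

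**The case against.** The strongest reply is that the trial's real test is the comparison of arms, and replacing the team does not bias it. Both arms pass from the same first six to the same second six, so a common shift cancels. This stands. A reader might infer from the complete change of staff that the treatment effect itself is confounded. The documents do not support that: it would need staff split by school or arm, and no section says they are. Nor should the conditional risk be enlarged. An added SD of 1.41t would follow from exactly one operator per school (variance t²/2 per arm and wave, 2t² in all), but the protocol has six staff per wave, not four.

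The second reply is that the team shift should be small. Rest, posture, arm support, footwear and pocket contents are scripted, the instruments are common and calibrated daily, the monitor is automated, and the week of training aims at differences between and within observers. This also stands, and most clearly for weight. It bears on the size of the shift, not on whether it can be separated from change. The protocol describes no check of agreement between the two teams.

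Third, uncontrolled six-month change in students aged 14 to 19 already mixes growth, season and habituation to measurement, and a spurious shift would also appear in the control arm. Both are true. They are reasons for not drawing effectiveness conclusions from within-group change at all. Using the control arm to expose the shift is already the between-arm comparison.

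Finally, a separate team was chosen against observer bias. Section 3.10 also has unspecified health staff helping to train teachers in the intervention schools, which could reveal allocation. A fresh team is a defensible safeguard, so the documents do not support insisting that the same six be kept.

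**Conclusion.** The point holds in a limited form. As written, within-group change in weight, BMI and blood pressure is fully confounded with the change of measuring team. The effectiveness claims built on it in objective 5 and hypotheses 8 and 9, and the paired tests of them, cannot be interpreted. Under the assumed SD of 10 mmHg (8 to 12), a 1 mmHg shift alone produces a significant paired test about 54% of the time (40% to 73%). The size of the shift is an assumption, and the protocol's safeguards should keep it low.

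The between-arm and group-by-time comparison is not confounded by the replacement as such. It is exposed only if measurers are divided by school or arm, which the protocol leaves open. With three separate operators per arm, the added SD would be about 1.15 times the operator SD. The outcomes are secondary, and the remedy is cheap enough that the gap should be closed before measurement begins.

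**What to change.** - **Sections 3.10 and 3.11:** require each measurer in each wave to measure an equal share of students in all four schools.
- **Appendix A, Sections 9 and 10:** add a measurer code to the form.
- **Sections 1.5.2 (objective 5), 1.6 (hypotheses 8 and 9) and 3.17.3:** base effectiveness for weight, BMI and blood pressure on the between-arm (group-by-time) contrast only, and report within-group change descriptively.

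The cost is that each measurer travels to all four schools, plus one extra field on the form. No additional staff are needed.

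Keeping the same six measurers at both visits is optional. It would remove the change of team, but it is acceptable only if those staff take no part in teacher training in the intervention schools and remain unaware of allocation.

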**3.11 Intervention**

At this stage permissions and consent would had been sought from the Ministry of Education, District Directors of Education, Chairmen of the Parent Teacher Associations, parents/guardians, and students to carry out the study. All materials for the study will be ready at this stage. The objectives of the study and the eligibility criteria to participate in this study will be explained to all the students’ involved. Students will go through medical check-up which will be carried out by the two clinicians in order to pass eligibility criteria to be enrolled into the study.

The self-administered questionnaire will be given to students to complete. Health staff will measure students anthropometric and blood pressure measurements. Confidentiality and anonymity will be assured at all stages of the study. The module will be implemented in the intervention schools for a period of six months but not in the control schools. Then at the end of six months the same questionnaire will be given to students in both the intervention and the control schools. Health staff who will not take part during the baseline data collection will take anthropometric and blood pressure measurements of students at post intervention study. A total of 848 students will participate in the study; intervention (424) and the control (424) schools. Contamination of the intervention will be prevented by having intervention and control schools with distances between them.

**3.12 Data Collection**

Data will be collected using validated and pre-tested questionnaire. Data will be collected at baseline and at six months post intervention where socio-demographic data, physical activity score, smoking, alcohol consumption, dietary intake, height, body weight, diastolic and systolic BP, CVD knowledge, motivation and behavioral skills scores will be collected.

**3.12.1 Study Instruments**

A self-administered questionnaire, which will be validated and pre-tested will be used to collect data. Weight and height scales will be used to collect data on body weight and height measurements of students respectively. Then a diastolic and systolic apparatus will be used to measure blood pressure of participants. Body weight, height, diastolic, and systolic blood pressure measurements will be taken by the health staff.

**3.12.2 Questionnaire**

The questionnaire will be pre-tested and assisted self-administered questionnaire in English language as in Appendix. The questionnaire will be divided into ten sections namely, socio demography, dietary intake, smoking, alcohol consumption, physical activity, CVD knowledge, motivation, behavioral skills, BMI (weight and height), and blood pressure (diastolic and systolic). The questionnaires will be administered in a classroom setting in all the selected schools.

Section one of the questionnaire will be used to access students’ age, gender, grade, ethnicity, monthly pocket money, and family history. Data on age will be collected in the form of open ended question and students will fill in the blank space provided. The rest (ethnicity, gender, religion, and family history) are in the form of closed ended questions and students are to choose the answers that will pertained to them.

Section two is a seven-day dietary recall instrument which are foods items mostly consumed in Ghana, the Ghana Demographic and Health Survey, (GDHS), (GSS, 2009; Nti, 2008) to assess dietary consumption. Amounts of each food intake will be stated with the use of handy measure tables (food weights). This are based on the weights of foods with their equivalent handy measure tables which are commonly used

in Ghana (Owusu, Ankrah, Boateng, & Anteh, 1995). Then frequency of consumption of certain foods will be scored based on one (1) for never dietary consumption, two (2) for 2-3 times per week, three (3) for 4-5 times per week, four (4) for 6 times per week, and five (5) for daily intake of a particular food item.

Section three and four are the modified smoking and alcohol questionnaires, Global Youth Tobacco Survey (GYTS) developed by WHO and Centre for Disease Control and Prevention (CDC) (CDC, 2008). It is a school-based adolescents’ self- administered questionnaire which comprised of a set of core questions that will be used to evaluate tobacco and alcohol control and prevention programmes among secondary school students. Students would be classified as never, ever, and current smokers and alcohol consumption. Strict confidentiality will be ensured among researchers to avoid disclosure of smoking and alcohol statuses to school authorities, teachers, or parents.

Section five consists of physical activity questionnaire (PAQ-A) for secondary school students (Kowalski, Crocker, & Donen, 2004). This is a 7-day recall instrument which will be administered in a classroom setting to assess general levels of physical activity among secondary school children. Students will be informed before this section is administered that is not a test but a tool for assessing actual physical activity during the past seven (7) days. Each physical activity item will be scored on a five (5) point scale. The value from one (1) to five (5) for each of the items used in the physical activity composite score, then the mean of the items which resulted in the final PAQ-A activity summary score.

Section six will be the modified CVD knowledge assessment questionnaire which comprise of meaning of CVDs, risk factors and preventive strategies of CVDs to assess CVD knowledge score among respondents. The school-based instrument was developed by George et al. (2013) to assess CVD knowledge levels among students. The scoring of the instrument is in the form of true or false questions and unsure (don’t know) response for each question. Respondents are to choose either true, false or ‘’don’t know’’ by circling in the provided box. Each correct answer will be awarded one score. The maximum score is 26 and the minimum score is 0.

Section seven and eight are the Motivation and Behavior skills respectively, which are the modified versions of the LifeWindows Information-Motivation-Behavioral skills questionnaires (The LifeWindows Team, 2006) which constructs were originally developed by (Fisher, Fisher, Amico, & Herman, 2006). Motivation constructs assess questions on personal and social motivation relating to how motivated or encouraged participants are to perform a CVD risk factor reduction lifestyle. Scoring of responses are based on the likert scale from ‘I strongly disagree to I strongly agree’. Each of the items are scored based on the responses from 0 to 3;

with strongly disagree as 0 to strongly agree as 3. All reverse items will be scored asuch before the final scores are determined.

Behavioral skills questionnaire will test students’ ability to reduce CVD risk factors. The questions will assess their behavior skills including how hard or how easy is to apply their behavioral skills. The responses are ‘very hard to very easy’ with a scale from 0 to 3. Very hard is awarded a score of 0 while very easy has a score of 3. Then the mean scores will be determined.

